### 10.5 Contraindication of concurrent use

The use of the following medical devices and medicines is prohibited during the study period.

- (1) Anti-adhesion products other than the investigational products for this clinical trial
- (2) Antithrombotic/anticoagulant drugs
- (3) Systemic corticosteroids : Continuous use of 2 mg/kg (20 mg/day) as prednisolone for 7 days or more, or equivalent dose of a corticosteroid

## 11. Observation and clinical testing items, and their methods

【Schedule of Clinical Study】

| Item            | Screening | Application and Evaluation |         |          |
|-----------------|-----------|----------------------------|---------|----------|
| Visit           | Visit 1   | Visit 2                    | Visit 3 | Visit 4  |
| Day             | -30~0     | Day 0                      | Day 7±3 | Day 42±7 |
| Written consent | ●         |                            |         |          |

|                                                |   |                   |   |   |
|------------------------------------------------|---|-------------------|---|---|
| Inclusion/exclusion criteria                   | ● |                   |   |   |
| Demographic survey/physical examination        | ● |                   |   |   |
| Vital signs test                               | ● |                   |   | ● |
| Medical/administering history    | ● |                   |   |   |
| Subjects enrollment                            |   | ●                 |   |   |
| Surgery and applying investigational product   |   | ●                 |   |   |
| Esophagography                                 |   |                   |   | ● |
| Evaluating adhesion scores                     | ● |                   | ● | ● |
| Urine $\beta$ -HCG testing (for fertile women) | ● |                   |   | ● |
| Hematological test                             | ● |                   | ● | ● |
| Serum biochemical test                         | ● |                   | ● | ● |
| Urinalysis                                     | ● |                   | ● | ● |
| Collecting concomitant drug      | ● | ●                 | ● | ● |
| Collecting adverse event         |   | ● (After surgery) | ● | ● |

(1) Collect medical history within 5 years before participating in the clinical trial.

(2) Collect information on drugs that have been administered within 4 weeks of the screening visit or are currently being administered.

(3) Adverse events should be followed up until the symptoms disappear, and if it is difficult for a subject to visit, the follow-up should be performed by phone. (However, if a subject is diagnosed with hypothyroidism or hypoparathyroidism through thyroid function test after thyroidectomy, the resulting adverse events should be followed up until the last visit of the subject for the clinical trial.)

#### ☐ Efficacy evaluation

(1) Primary efficacy endpoint : Comparison of esophageal movement

To assess the degree of adhesion, compare the esophageal movement of the test group and the control group through Marshmallow esophagography 6 weeks after surgery.

(2) Secondary efficacy endpoint : Adhesion Scores

Evaluate adhesion scores through surveys at screening, 1 week after surgery, and 6 weeks after surgery, and compare the test group and the control group.

☐ **Safety evaluation**

Investigate all adverse events at every visit after surgery.

## **11.1. Observation and clinical testing items**

### 1) Visit 1 : Screening (Day -30~0)

Subjects who have agreed to participate in this clinical trial should be screened to ensure that they are eligible to participate in the study.

- Receive informed consent
- Review inclusion/exclusion criteria
- Demographic survey/physical examination : Date of birth, gender, weight, height, etc.
- Vital signs test : Blood pressure, pulse rate
- Medical/administering history : Diabetes mellitus, hypertension, stroke, ischemic heart disease, malignant tumor, acute infection, allergy, and whether taken bisphosphonate, etc.
- Evaluate adhesion scores
- Urine  $\beta$ -HCG testing (only for women with childbearing age)
- Hematological test : RBC, Hemoglobin, Hematocrit, Platelet, WBCs, Neutrophil, Lymphocyte, Monocyte, Eosinophil, Basophil, Blood coagulating time (PT/APTT)
- Serum biochemical test : sodium, Potassium, Chloride, Creatinine, BUN, ALT, AST,ALP, Total Bilirubin, Albumin, Total Protein, Total Cholesterol, Glucose
- Urinalysis : pH, Specific gravity, WBC, Protein, Bilirubin, Glucose, Urobilinogen, Ketone, Nitrite, Blood
- Collect concomitant drugs

### 2) Visit 2 : Day 0

- Perform a surgery and apply an investigational product
- Enroll subjects
- Collect concomitant drugs
- Collect adverse events : After surgery

### 3) Visit 3 : Day 7 $\pm$ 3

- Evaluate adhesion scores
- Hematological test : RBC, Hemoglobin, Hematocrit, Platelet, WBCs, Neutrophil, Lymphocyte, Monocyte, Eosinophil, Basophil, Blood coagulating time (PT/APTT)
- Serum biochemical test : sodium, Potassium, Chloride, Creatinine, BUN, ALT, AST,ALP, Total Bilirubin, Albumin, Total Protein, Total Cholesterol, Glucose
- Urinalysis : pH, Specific gravity, WBC, Protein, Bilirubin, Glucose, Urobilinogen, Ketone, Nitrite,

#### Blood

- Collect concomitant drugs
- Collect adverse events

#### 4) Visit 4 : Day 42±7

- Check vital signs
- Esophagography
- Evaluate adhesion scores
- Urine β-HCG testing (only for women with childbearing age)
- Hematological test : RBC, Hemoglobin, Hematocrit, Platelet, WBCs, Neutrophil, Lymphocyte, Monocyte, Eosinophil, Basophil, Blood coagulating time (PT/APTT)
- Serum biochemical test : sodium, Potassium, Chloride, Creatinine, BUN, ALT, AST,ALP, Total Bilirubin, Albumin, Total Protein, Total Cholesterol, Glucose
- Urinalysis : pH, Specific gravity, WBC, Protein, Bilirubin, Glucose, Urobilinogen, Ketone, Nitrite, Blood
- Collect concomitant drugs
- Collect adverse events

## 11.2 Observation method

### 11.2.1 Signing informed consent

Prior to conducting this clinical trial, the investigator shall explain the contents of the 'Informed Consent Form' to the subjects or their legal representative, etc., only for subjects judged to meet the inclusion criteria, and ensure that the subjects or their legal representative, etc. understand the contents well. And then, the investigator shall obtain the written consent to participate in the clinical trial at their will. In addition, the date of signing the consent shall be recorded in the Case Report Form.

### 11.2.2 Demographic and medical history survey

Prior to conducting the clinical trial, check the subject's demographic information and medical/administering history, including the followings, through interviews, medical charts, and questions, and record them in the Case Report Form.

- Demographic survey : Date of birth, gender
- Physical examination and vital signs: Weight, height, blood pressure, pulse rate
- Medical history : Medical conditions that can affect surgery or anesthesia, such as diabetes mellitus, hypertension, stroke, ischemic heart disease, osteoarthritis, gout, hyperuricemia, sleep apnea syndrome, gallbladder disease, back pain or peripheral blood disorder

- Testing : Hematological test/serum biochemical test/urinalysis etc.
- Others : Whether taking drugs, smoking, drinking, pregnancy status and plan

#### 11.2.3 Evaluation on subject eligibility

Evaluate whether the subject meets the inclusion and exclusion criteria through demographic survey, medical history, past clinical records (medical charts), and questionnaires.

#### 11.2.4 Assignment of subject identification code

Assign a subject identification code sequentially only to subjects who agree to participate in the clinical trial and meet the inclusion/exclusion criteria according to the following method, and write the "Screening/Enrollment log." The subject identification code is used as an identification code along with the randomization code and subject initials.

- Institution: Severance Hospital (S01), Kangbuk Samsung Medical Center (S02), Seoul St. Mary's Hospital (S03)
- Subject Identification Code: Institution code-Enrolled order

Ex) Subjects enrolled in Severance Hospital: S01-001, S01-002...

Subjects enrolled in Kangbuk Samsung Medical Center: S02-001, S02-002...

Subjects enrolled in Seoul St. Mary's Hospital: S03-001, S03-002

### 11.3 Randomization method

#### 11.3.1 Randomization

For randomization, make sure that subjects are assigned to the test group and the control group at a ratio of 1:1 by the block randomization method. It will be generated using SAS by a statistical expert who is not directly related to the institution. For blinding, before the study is terminated, only a minimum number of personnel who are not directly related to the institution should be able to access to the randomization table and code. Subsequently, the institution shall finally assign a randomization number (3-digit number) to the subjects who meet the inclusion/exclusion criteria through screening. This randomization code, together with the subject identification code specified in 11.2.4, will be used as the subject identification code during the clinical study.

Ex.: Randomization code

[figure not shown]

2nd, 3rd digits – sequentially

1st digit – institution code (Severance 1, Kangbuk Samsung 2, Seoul St. Mary's 3)

#### 11.3.2 Unblinding

A. Method of unblinding during the clinical trial

Use an unblinding sealed bag for unblinding during the clinical trial. The bag should be brown so that the contents are not shown when shining it in, and there should not be a hole to show the contents. And the signature should be on the sealed part so that it can be shown whether the unblinding sealed bag has been opened or not.

B. Situations requiring unblinding during the clinical trial

- ① When a serious adverse event occurs, if information how to deal with it is required, unblinding can be performed.
- ② In the event of a Suspected Unexpected Serious Adverse Reaction (SUSAR), unblinding must be performed.

C. Procedure of unblinding during the clinical trial

- ① The unblinding sealed bag should be delivered to the PI prior to initiating the clinical trial and should not be accessed by anyone other than the person concerned. In addition, it should be stored close to the PI.
- ② When unblinding, the information should be delivered directly to the person who performs medical treatment which requires the information, and no other researchers or related persons should be informed of randomization except where necessary.
- ③ In the event of a situation requiring unblinding, write the information on the subject and researcher, date of unblinding, reason for unblinding, etc. in 'Document on Unblinding', the source document, and CRF. Also, the signature of the person who performed the unblinding, the date and time of unblinding, etc. should be recorded on the outside of the bag.
- ④ Deliver the written 'Document on Unblinding' to the sponsor by e-mail or fax.
- ⑤ All unblinding sealed bags should be collected by the PI at the end of the clinical trial.

D. Unblinding after the completion of the clinical trial

- ① Blinding should be maintained before the database is officially locked for statistical analysis.
- ② Once the analysis set is determined after the blind review, the person in charge of producing (or labeling) the investigational product shall deliver the product code to the person in charge of creating the randomization code, and the person in charge of creating the randomization code shall deliver the randomization code, containing the actual group instead of the product code, to the person in charge of analysis.

#### 11.4 Independent evaluator's evaluation

The evaluator of the institution who evaluates the esophagography (primary endpoint) and adhesion scores shall conduct and evaluate surveys of esophagography and adhesion scores while being blinded. And the independent evaluator should be blinded to the treatment group assignment of the subjects so that the independent evaluator can make an objective judgment.

### 11.5 Primary endpoint: Comparison of esophageal movement using Marshmallow esophagography

After 6 weeks of thyroidectomy and application of the investigational product, ask the patient to take a prone position. Instruct the patient to swallow a mass of 20 mm diameter marshmallow with liquid barium sulfate (Solotop Sol. 140), then observe the marshmallow's passage through the esophagus by fluoroscopy [24,25,26].

First, measure the esophageal passage time of the marshmallow in the prone position, and classify it into normal and abnormal based on 30 seconds. When the marshmallow gets stuck in a part of the esophagus and does not move for more than 30 seconds, it is defined as an impaction. If an impaction has occurred in the prone position, ask the patient to change the posture to standing position and swallow his/her saliva, then observe the movement of the marshmallow in the esophagus. With this test, evaluate the marshmallow's passage pattern in the esophagus by dividing them into 4 grades as shown in the following table [24].

| Score | Definition | Esophageal passage time of marshmallow                                                                       |
|-------|------------|--------------------------------------------------------------------------------------------------------------|
| 3     | Normal     | Passed through the esophagus within 30 seconds in the prone position                                         |
| 2     | Minor      | Passage time exceeds 30 seconds in the prone position; and passed within 30 seconds in the standing position |
| 1     | Moderate   | Impacted in the prone position; and passage time exceeds 30 seconds in the standing position                 |
| 0     | Severe     | Impacted in both the prone and standing positions                                                            |

### 11.6 Secondary endpoint: Adhesion Scores

Evaluate adhesion scores through surveys at screening, 1 week and 6 weeks after thyroidectomy and application of the investigational product. Score each clinical symptom for all questionnaires on a scale of 0 to 10. The higher the score, the more severe the adhesion [24,27].

| Evaluation item                      |                                                                                                |
|--------------------------------------|------------------------------------------------------------------------------------------------|
| Subjective discomfort of patient     | 1. Do you have trouble swallowing your saliva?                                                 |
|                                      | 2. Do you have difficulty swallowing water?                                                    |
|                                      | 3. Do you have any difficulty in swallowing hard foods?                                        |
|                                      | 4. Are your neck wrinkles abnormal in your own opinion?                                        |
| Objective evaluation of investigator | 5. Are the wrinkles on the neck symmetrical and natural when the patient is at rest?           |
|                                      | 6. Are the wrinkles on the neck symmetrical and natural when the patient is at neck extension? |

---

7. What is the degree of inflammatory response or scar formation based on the surgical findings?

---

What is the neck extension? : A condition in which the subject's jaw is usually directed upward at 30 to 45 degrees from the horizontal so as not to be uncomfortable when the subject extends his/her neck

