## 10. Procedure (usage, method of use, period of use, combination therapy, etc.)

### 10.1 Study design

☐ A prospective confirmatory clinical trial of double-blinded (subjects-evaluator), multi-center, randomized and non-inferiority

☐ Experimental product (test group) : MegaShield

☐ Comparator (control group) : Guardix-SG

This is a prospective confirmatory clinical trial of double-blinded (subjects-evaluator), multi-center, randomized and non-inferiority which is performed by setting the test group and the control group. Subject identification codes are assigned only to subjects who are judged to meet the inclusion/exclusion criteria among those who are in need of total thyroidectomy. In addition, subjects are given a randomization code (3 digits) in order according to the randomization table and assigned to the corresponding application group. The randomization code and subject identification code will be used as the subject number during the clinical trial.

(For details, see 11.2.4 Assignment of subject number and 11.3.1 Randomization.)

This clinical trial is a double-blind trial, and both subjects and evaluator should be blinded. The evaluator is an independent evaluator and does not participate in surgery, so it is not possible for him/her to know which investigational product was applied to the subject. And since he/she contacts the subject only during evaluation, blinding will be maintained. Since the subject is applied with the assigned investigational product while under general anesthesia during surgery, he/she cannot know which investigational product has been applied, and does not know even after the surgery. Thus, subjects and the independent evaluator are blinded during the clinical trial.

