## 14.2 Secondary efficacy endpoint

The secondary endpoint is adhesion scores.

Evaluate adhesion scores through the following surveys at screening, 1 week and 6 weeks after thyroidectomy and application of the investigational product.

The secondary endpoint is evaluated by providing descriptive statistics (mean, standard deviation, median, minimum and maximum) by time point and group, and by providing descriptive statistics of the mean changes, compared to those at the screening, for each time point and each group after surgery. For the mean and mean variance of the intergroup at each time point, the unpaired t-test or Wilcoxon ranksum test is applied depending on whether the normality assumption is satisfied (Shapiro-Wilk test), and for the mean variance of the intragroup, the paired t-test or Wilcoxon signed rank test is applied. The significance level for each statistical analysis is  $p < 0.05$ .

Evaluate adhesion scores through surveys at screening, 1 week and 6 weeks after thyroidectomy and application of the investigational product. Score each clinical symptom for all questionnaires on a scale of 0 to 10. The higher the score, the more severe the adhesion [24,27].

|                                      |                                                                                                                                                                                                                                                                                            |
|--------------------------------------|--------------------------------------------------------------------------------------------------------------------------------------------------------------------------------------------------------------------------------------------------------------------------------------------|
| Subjective discomfort of patient     | 1. Do you have trouble swallowing your saliva?
2. Do you have difficulty swallowing water?
3. Do you have any difficulty in swallowing hard foods?
4. Are your neck wrinkles abnormal in your own opinion?                                                                        |
| Objective evaluation of investigator | 5. Are the wrinkles on the neck symmetrical and natural when the patient is at rest?
6. Are the wrinkles on the neck symmetrical and natural when the patient is at neck extension?
7. What is the degree of inflammatory response or scar formation based on the surgical findings? |

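### Adhesion score: items 5 and 6 are worded against the stated severity direction, and item 7 has no surgical findings to rate at screening

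*Protocol*

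**What the plan says.** Adhesion score is the only secondary efficacy endpoint. Protocol sections 11.6 and 14.2 list the same seven items. The common scoring instruction is "Score each clinical symptom for all questionnaires on a scale of 0 to 10", followed by "The higher the score, the more severe the adhesion".

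- **Items 1 to 4**, answered by the patient, ask about trouble or difficulty with swallowing and about the look of the neck: "Are your neck wrinkles abnormal in your own opinion".
- **Items 5 and 6**, in the investigator's block, ask "Are the wrinkles on the neck symmetrical and natural when the patient is at rest" and "Are the wrinkles on the neck symmetrical and natural when the patient is at neck extension".
- **Item 7**, in the same block, asks "What is the degree of inflammatory response or scar formation based on the surgical findings".

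Section 14.2 sets the timing: "Evaluate adhesion scores through the following surveys at screening, 1 week and 6 weeks after thyroidectomy". It then plans between-group comparisons at each time point, and of the change from screening, plus within-group tests of that change, all at the 5% level. Section 11.1 places screening on Day -30 to 0, and section 8.1 admits only patients having their first thyroidectomy. Section 11.4 assigns the rating of adhesion scores to a blinded evaluator. Section 10.1 adds: "The evaluator is an independent evaluator and does not participate in surgery". Section 11.2.4 names three institutions.

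**The concern.** For items 5 and 6 the question and the general rule point in opposite directions. A rater who answers the question gives a high number to a good neck; a rater who follows the rule gives it a low one. The protocol has no anchors and no reverse-scoring instruction to settle which applies. An analysis plan can flip a scale only if everyone used it the same way round. Once ratings have been taken in mixed directions, it cannot separate them from the numbers alone.

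Item 7 has a different fault. It calls for surgical findings at a visit before any thyroid operation, and no rule omits it there or gives it a fixed value. After surgery the schedule contains no second operation, so the material on which the evaluator should base the rating at weeks 1 and 6 is not stated.

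At stake is the meaning of three of the seven items, which make up the whole observer-rated block, and of any total or subscore that contains them.

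**Working it through.** **Plan's own figure.** The protocol gives no figure for the adhesion score. Its one reproducible calculation is the sample size in section 8.4: 2(1.96 + 0.84)² × 0.2² / 0.1² = 62.72 (printed as 62.8), rounded up to 63; 63 / 0.9 = 70 per group. It reproduces, and nothing below changes it, because the secondary endpoint does not enter it.

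**Direction, item by item, against the stated rule (high = worse).**

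| Item | What a high answer to the question means | Fits the rule? |
|---|---|---|
| 1–3 | more trouble swallowing | yes |
| 4 | more abnormal wrinkles | yes |
| 5, 6 | more symmetrical, more natural wrinkles | no |
| 7 | more inflammation or scar | yes |

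Items 4 and 5 ask about the same feature with opposite polarity.

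**Item 7 by visit.** At screening there has been no thyroidectomy (sections 8.1 and 11.1), so there are no surgical findings. At weeks 1 and 6 there is no new operation, and the rater was not present at the first one (section 10.1). If the item is left blank at screening, its change from screening does not exist, and a seven-item total would gain up to 10 points with no screening counterpart. If it is set to 0, the change equals the postoperative rating. The protocol chooses neither.

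**Size, if the items were summed.** This is an assumption; the protocol does not say how items are combined. Items 5 and 6 are taken as rated literally by everyone.

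1. Range. Best neck: 0+0+0+0+10+10+0 = 20. Worst neck: 10+10+10+10+0+0+10 = 50. With aligned items the range is 0 to 70.
2. Uniform effect of d per item. Literal: 5d − 2d = 3d. Aligned: 7d. Share kept: 3/7 = 43%.
3. Investigator block only (items 5 to 7), 1 point worse on each. Literal: −1 − 1 + 1 = −1. Aligned: +3. The sign flips.
4. Standardized effect, assuming equal item SDs and a common inter-item correlation ρ. In units of the item variance, the aligned total has variance 7 + 42ρ and the literal total 7 + 2ρ. The share of the standardized effect kept is (3/7) × √[(7 + 42ρ)/(7 + 2ρ)].

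| ρ (assumed) | Share kept |
|---|---|
| 0 | 43% |
| 0.3 | 69% |
| 0.5 | 80% |
| 0.7 | 89% |

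**Size, if items 5 and 6 are analysed singly.** Let a share p of patients in each group be rated literally. The group difference on the item is then (1 − p)d − pd = (1 − 2p)d. It is intact at p = 0, absent at p = 0.5 and reversed at p = 1. Items 1 to 4 are unchanged in every case.

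**The case against.** The strongest reply is that the general rule already settles the direction. Items 1 to 6 are all phrased as yes/no questions, so the 0-to-10 meaning must come from the rule, and a careful rater would score items 5 and 6 by degree of asymmetry. Anchors may also stand in the case report form, which is not at hand. This much stands: a reader might infer that 20 of the 70 points are reversed, or that 57% of the effect is lost, and the documents support neither. Reversal is a risk created by conflicting instructions, and the loss needs both a sum and literal scoring by all raters.

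On item 7, an assessor could rate 0 before surgery, and the surgical findings may simply mean what is visible at the operated site. Comparisons at each postoperative time point need no screening value. All of this is plausible, but the protocol does not say it.

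Two further inferences are tempting. One is that item 7 feeds the surgeon's unblinded knowledge into the rating. Nothing tells the evaluator to seek it, and sections 10.1 and 11.4 point the other way. The other is that the investigator heading over items 5 to 7 contradicts section 11.4. The definition in section 19.3 does not prevent a sub-investigator from acting as the blinded evaluator, so this is at most a matter of labelling.

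**Conclusion.** The point holds as a contradiction between a stated scoring rule and the wording of items 5 and 6, and as an item 7 with no screening basis and no stated source afterwards. It covers items 5 to 7 and any total or subscore containing them. It does not make the whole secondary endpoint invalid: items 1 to 4 are sound singly and have usable screening values.

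The effect ranges from none, if every rater followed the severity rule, to a reversed sign on items 5 and 6 and on the investigator block, if all read the questions literally. For a seven-item total in that latter case, 43% to 89% of the standardized effect remains, assuming equal effects and equal SDs on all items and ρ between 0 and 0.7.

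This should be fixed, because it concerns the only secondary efficacy endpoint and mixed ratings cannot be untangled later from the numbers alone. It is not critical: the non-inferiority decision in section 14.1 rests on the esophageal movement score, and the margin and sample size are untouched.

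**What to change.** 1. Reword items 5 and 6 in sections 11.6 and 14.2, and on the case report form, in the severity direction with explicit anchors: 0 = fully symmetrical and natural, 10 = most asymmetrical or unnatural.
2. State that item 7 is rated by the blinded evaluator from findings visible at the surgical site at weeks 1 and 6. Either leave it out of the screening score and of change from screening, or fix its screening value in advance. If it is left out, a summed change would rest on items 1 to 6, with an aligned range of 0 to 60.
3. For data already collected, establish under blinding how each rater scored items 5 and 6, and document this before any recoding. Do not apply 10 − x across the board, since that would reverse correct scores from raters who followed the severity rule. Where a rater's usage cannot be established, report those items as uninterpretable and leave them out of any total.

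The cost is a wording amendment, a revised form, brief rater instruction at three sites and, if enrolment has begun, a blinded query to each rater. Sample size and the primary analysis do not change.
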